#### Data analysis

The data will be analyzed using SPSS version 17.0 software. The patients found to be eligible but not included in the study will be described and compared with the included patients. The patients who present at least one of the following conditions will be not in the final analysis: patients inappropriately included despite not providing consent and patients who remove their consent. The full analysis population (including all subjects who will be randomized and will be at least evaluated at baseline) will be used in the primary analysis, and the per-protocol population (including all subjects who will be randomized and will not have major protocol deviations) will be used in the secondary analysis to assess the robustness of the results. No interim analysis is planned. The normality of these parameters will be estimated using frequency histograms and the Shapiro test. The baseline parameters will be described for the two groups (“control” and “intervention”).

The analysis of the primary endpoint will consider the proportion of DGF for each group. These proportions will be compared using the chi^2^ test or Fisher’s exact test for categorical variables (primary analysis). Multivariate analysis (secondary analysis) using logistic regression models will be performed to determine variables potentially linked to DGF (donor’s variables: age, norepinephrine use, diabetes, high blood pressure; procurement variables: cold and warm ischemia durations; recipient’s variables: weight, dialysis duration).

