### Selection of participants

➢ Donor inclusion criteria○ Brain death with a beating heart○ Age between 18 and 70 years➢ Donor exclusion criteria○ Contra-indications for organ harvesting (infections, cancer, etc.)○ Chronic kidney disease○ Refusal of organ donation by the donor (confirmed by the French National Register or reported by the next-of-kin)○ Inclusion in another protocol➢ Recipient inclusion criteria○ Age between 18 and 70 years○ Indication of kidney transplantation○ Written informed consent given➢ Recipient exclusion criteria○ Indication of double kidney transplantation○ Indication of multiorgan transplantation

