### Outcomes

➢ Primary outcome: rate of DGF defined by the need for at least one dialysis session within the first 7 days after kidney transplantation➢ Secondary outcomes:○ Rate of SGF defined by a urine output of less than 1000 mL on day 1 after transplantation, or a decreased of less than 30 and 70% in creatinine plasma concentration, respectively, on days 3 and 7 after transplantation○ Combined rate of DFG + SGF○ Mild DGF defined by a serum creatinine reduction ratio from post-transplant day 1 to day 2 less than or equal to 30% plus 24-h urine creatinine excretion on day 2 greater than 1000 mg○ Severe DGF defined by a serum reatinine reduction ratio from post-transplant day 1 to day 2 less than or equal to 30% plus 24-h urine creatinine excretion on day 2 less than or equal to 1000 mg○ Duration of in-hospital length of stay (post-transplantation hospitalization)○ Daily urine output on days 1, 3 and 7○ Creatininemia and estimated creatinine clearance by the Modification of Diet in Renal Disease (MDRD) formula [17] on days 1, 3 and 7○ Rate of primary graft dysfunctions on day 1 defined by the absence of immediate renal function (anuria)○ Time between transplantation and normalization of graft function in patients presenting a DGF○ Function of kidney transplants at 1 year: kidney graft dysfunction defined by a clearance creatinine less than 30 mL min^−1^ estimated by the MDRD formula or total dysfunction defined by a persistent hemodialysis○ In-hospital and 1-year mortality rate of transplanted patients

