### Data registration

Data will be entered into the web-based electronic Case Report Form (eCRF) (RedCap, Vanderbilt University, Nashville, TN, USA) by trial or clinical personnel under the supervision of the trial site investigators at each participating center. The following data reported to influence the outcome of kidney transplantation will be registered at the different stages of the procedure:➢ In donors with a beating heart:○ Demographic data (age, sex, Body Mass Index (BMI), ethnic group, cause of death)○ Significant medical history (chronic kidney disease, hypertension, diabetes, alcohol abuse)○ Detailed SOFA score in the last 24 h before organ harvesting○ Significant biochemical abnormalities: hypernatremia > 160 mmol L^−1^, coagulation abnormalities (disseminated intravascular coagulation)○ Renal function, assessed by blood urea nitrogen levels, creatininemia and 24-h creatinine clearance in the last 24 h prior to the harvesting○ Immunological and viral status: Epstein-Barr virus (EBV) serology, number of HLA incompatibility➢ During kidney harvesting, preservation and transplantation○ Preservation data: type of preservation solution, use of a perfusion machine, cold ischemia time○ Intraoperative data: hemodynamic stability (systolic blood pressure < 80 mmHg, need for vasopressors), warm ischemia time, technical problems (duration of anastomose, surgical difficulties, hemorrhage)➢ In transplanted patients○ Demographic data (age, sex, BMI, blood group, ethnic characteristic)○ Significant medical history: hypertension, cardiac failure, diabetes, cause of the kidney disease, previous transplantation(s), duration of dialysis before transplantation, duration on the transplantation waiting list○ Viral (C hepatitis) and immunological (anti-donor antibodies) status○ Dialysis during the first week after transplantation○ Creatininemia and estimated creatinine clearance (MDRD) on days 1, 3 and 7 after transplantation○ 24-h urine output on days 1, 3 and 7 after transplantation○ Recipient and graft survival at 1 year

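### Recipients who withdraw consent at any time are dropped from the final analysis, so day-7 outcomes already observed are lost; the effect is probably small and the repair is cheap

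*Protocol article*

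**What the plan says.** All of this is in the protocol article.

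- **Exclusion rule (Data analysis).** "The patients who present at least one of the following conditions will be not in the final analysis". The conditions are "patients inappropriately included despite not providing consent and patients who remove their consent". Nothing says when the withdrawal must occur, and nothing keeps data gathered before it.
- **Population for the main comparison (Data analysis, next sentence).** The sentence reads, in part: "The full analysis population (including all subjects who will be randomized and will be at least evaluated at baseline) will be used in the primary".
- **Who consents (Selection of participants).** "Written informed consent given" is a recipient inclusion criterion, so the rule acts on recipients.
- **Primary outcome (Outcomes).** "rate of DGF defined by the need for at least one dialysis session within the first 7 days after kidney transplantation".
- **Recording (Data registration).** "Dialysis during the first week after transplantation" is an item of the electronic case report form.
- **Later follow-up (Outcomes).** "In-hospital and 1-year mortality rate of transplanted patients" is a secondary outcome, as is graft function at 1 year.

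**The concern.** The primary outcome closes at day 7, but a recipient stays in the study for a year. Someone who withdraws at month 3 or month 9 already has a known and recorded dialysis status. Read literally, the rule deletes it. The full analysis population, defined as "including all subjects who will be randomized and will be at least evaluated at baseline", would on its own wording keep the same person.

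The two conditions in the rule differ in kind. Removing people who never consented is defensible. Removing everything already collected from someone who later stops taking part is a choice. Withdrawal happens after treatment and could depend on how the first week went. The exclusion can therefore depend on the outcome, which would distort the observed DGF rates, shrink the risk difference and discard usable information.

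**Working it through.** **Inputs from the Sample size section.** DGF 30% v 20%; two-sided alpha 0.05; power 80%; 294 per group evaluable (588 in total); 10% loss allowance; 648 enrolled, that is 324 per group.

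**Assumed, because the article gives no figure.** Withdrawal after day 7 by a proportion wD of DGF recipients and wN of the others: 6%/2%, 10%/3% and 20%/5%. Recipients are treated as independent, as the article's own calculation does.

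**Step 1: the article's own figure.** With pooled variance and no continuity correction,

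n = [1.960·√(2·0.25·0.75) + 0.842·√(0.3·0.7 + 0.2·0.8)]² / 0.10² = 293.2, rounded up to 294 per group, 588 in total.

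This matches. The 10% allowance gives 588/0.9 = 654 or 588 × 1.1 = 647; the stated 648 is close to both. Power is 80.1% at 294 per group and 83.8% at 324.

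**Step 2: observed rate after deletion.** In an arm with true rate p, the fraction kept is

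k = p(1 − wD) + (1 − p)(1 − wN),

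and the observed rate is p(1 − wD)/k. For 10%/3%:

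- placebo: k = 0.3·0.90 + 0.7·0.97 = 0.949; rate 0.270/0.949 = 28.45%
- intervention: k = 0.2·0.90 + 0.8·0.97 = 0.956; rate 0.180/0.956 = 18.83%
- difference: 9.6 points

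Of 294 per group, 294 × 0.051 ≈ 15 and 294 × 0.044 ≈ 13 known outcomes are deleted. From 324 the counts are about 17 and 14.

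**Step 3: power.** The same two-proportion formula is applied to the remaining numbers, first from the 324 enrolled per group with no other loss, then from 294 on the assumption that other losses have already used up the allowance.

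| Withdrawal, DGF / non-DGF | Observed rates | Difference (points) | Power from 324 | Power from 294 |
|---|---|---|---|---|
| none | 30.0% v 20.0% | 10.0 | 83.8% | 80.1% |
| 6% / 2% | 29.1% v 19.3% | 9.8 | 81.9% | 78.0% |
| 10% / 3% | 28.5% v 18.8% | 9.6 | 80.5% | 76.6% |
| 20% / 5% | 26.5% v 17.4% | 9.1 | 76.6% | 72.5% |

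**Step 4: what equal withdrawal leaves intact.** The observed odds in an arm are p(1 − wD)/[(1 − p)(1 − wN)]. If wD and wN are the same in both arms, they cancel in the ratio. The odds ratio stays at (0.3/0.7)/(0.2/0.8) = 1.714 in every row. With no true effect both arms have the same expected rate, so the test remains valid.

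**Step 5: what unequal withdrawal would do.** Take no true effect, 30% DGF in both arms, wN = 3% in both, and wD = 10% in one arm and 20% in the other. The observed rates are 0.270/0.949 = 28.45% and 0.240/0.919 = 26.12%, a false difference of 2.3 points. At 294 per group the two-sided type I error is about 9.4%.

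**The case against.** **The populations may not conflict.** The exclusion comes just before the population definitions and applies to the final analysis as a whole. It can be read as a general carve-out, with the populations drawn from whoever remains. That is a fair reading, so a reader who infers a flat contradiction goes further than the text allows. The deletion of observed outcomes stands on either reading.

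**The law or the consent form may require deletion.** The article says only that data are handled under French law, and the consent wording is not shown. The exclusion condition does not separate stopping follow-up from refusing use of data already held. This stands as a limit on what may be kept, and the fix has to respect it.

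**The loss allowance covers it.** In part. The 10%/3% case removes about 4.7% of recipients, and power from 324 per group stays above 80%. The lower column of power figures applies only if other losses have already consumed the allowance.

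**Blinding prevents bias.** A reader might infer that the rule inflates type I error. The article does not support that. Recipients, their clinicians and the statistician are blinded, the drug is given once and to the donor, and nothing suggests why withdrawal among DGF recipients should differ by arm. The 2.3-point case is an illustration of a mechanism, not an expectation. Blinding does not stop withdrawal from depending on DGF itself, but when that dependence is equal by arm it leaves the null test and the odds ratio alone.

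**The rates are invented.** They are assumptions. Recipients receive no study drug and the recorded follow-up looks light, so real withdrawal may be lower than any row of the table.

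**Conclusion.** The point holds in a limited form. As written, the rule deletes observed primary outcomes of recipients who withdraw between day 7 and 1 year. That is an avoidable exclusion after randomization, and its relation to the full analysis population needs clarifying.

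The effect is probably small. Under the assumed rates, with independent recipients and equal withdrawal by arm, the risk difference falls by 0.2 to 0.9 points. Power falls by about 2 to 7 points from 83.8%, and drops below 80% from full enrolment only in the most extreme case. A false treatment difference requires arm-specific withdrawal, for which the article gives no reason. This is a cheap improvement worth making, not a threat to the validity of the trial.

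**What to change.** Replace the withdrawal condition with a rule along these lines: exclude only recipients who never gave consent, or who object to the use of data already collected, as the consent wording and French law require. Keep every other withdrawing recipient in the full analysis population, in the arm allocated to their donor, with data up to withdrawal, including day-7 dialysis status where it is known. State that this exclusion is applied before the analysis populations are formed, so that the two sentences agree. Report withdrawals by arm and by day-7 status.

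The cost is a sentence or two in the analysis section, one line in the reporting tables, and a check that the consent wording permits retention. The sample size does not change. A few recipients who object to data use will still be lost.

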#### Sample size

The sample size was determined to obtain 80% power to detect a 10% difference for rate of DGF (as defined in the primary endpoint section) at day 7 between the two groups, as this difference is considered to be clinically significant. In accordance with previous studies [7, 8], we hypothesized that 30% of the patients in the placebo group and 20% of the patients in the intervention group will develop DGF. With the threshold for statistical significance set at a *p* value of 0.05 (two-sided alpha), these calculations showed that 588 participants (recipients) are needed (294 per group). Assuming that a potential 10% of participants will be lost to follow-up (for the primary or the secondary endpoints), a total of 648 recipients needs to be included. Secondary outcomes will be compared between the two groups: using the chi^2^ test or Fisher’s exact test for categorical variables and Student’s *t* test for continuous variables.

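### The primary DGF test is unadjusted although the plan names and records baseline predictors of DGF; this causes no bias but gives up a modest amount of precision

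*Protocol article*

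**What the plan says.** Under Outcomes, the primary endpoint is binary: "rate of DGF defined by the need for at least one dialysis session within the first 7 days after kidney transplantation". Under Data analysis, the primary comparison has no covariates: "The analysis of the primary endpoint will consider the proportion of DGF for each group", and "These proportions will be compared using the chi^2^ test or Fisher’s exact test for categorical variables (primary analysis").

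The same section then describes a second model: "Multivariate analysis (secondary analysis) using logistic regression models will be performed to determine variables potentially linked to DGF". Its candidate variables are:
- **Donor:** age, norepinephrine use, diabetes and high blood pressure.
- **Procurement:** cold and warm ischemia durations.
- **Recipient:** weight and dialysis duration.

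The text does not say that treatment is in this model or that it yields an adjusted treatment effect.

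Data registration introduces the case report form items with "The following data reported to influence the outcome of kidney transplantation will be registered". Its list includes donor age, hypertension and diabetes, and recipient BMI and duration of dialysis before transplantation.

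**The concern.** In a randomized comparison of a binary outcome, adjusting for baseline variables that predict the outcome raises power at a fixed sample size. It also takes chance imbalance in those variables out of the estimate. This plan identifies such variables and collects most of them, but uses them only to look for risk factors. They do nothing for the cyclosporine-placebo contrast.

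This is a stated choice and not a detail left to an analysis plan, because the article labels the chi-square or Fisher comparison as the primary analysis. At stake are a few points of power that need no extra recipients.

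**Working it through.** **1. Reproduce the planned size.** Inputs from Sample size: "30% of the patients in the placebo group and 20% of the patients in the intervention group will develop DGF"; "a *p* value of 0.05 (two-sided alpha"); and "The sample size was determined to obtain 80% power to detect a 10% difference for rate of DGF". With mean proportion 0.25 and no continuity correction:

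n per group = [1.96·√(2·0.25·0.75) + 0.8416·√(0.30·0.70 + 0.20·0.80)]² / 0.10²
= [1.96·0.6124 + 0.8416·0.6083]² / 0.01 = 293.2, so 294 per group and 588 in total, as stated.

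Power at n per group = Φ{[0.10·√n − 1.96·√0.375] / √0.37}.
- n = 294: Φ(0.846) = 80.1%.
- n = 324 (all 648 recruited and evaluable): Φ(0.986) = 83.8%.

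**2. Gain from adjustment.** The documents give no prognostic strength, so it is an assumption, shown as a range. The model is logistic with one standardized risk score, its intercepts solved so that the marginal rates stay at 30% and 20%. The variance ratio is that of the efficient adjusted risk difference to the crude one. Power follows from the formula above with n = 294/ratio, and the extra recipients are 588/ratio − 588 (from unrounded ratios). The last two columns are simulated: 8,000 trials per row, 294 independent recipients per group, Wald test for the adjusted model.

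| Assumed c-statistic | Variance ratio | Power by formula | Worth in recipients | Simulated crude | Simulated adjusted |
|---|---|---|---|---|---|
| 0.50 | 1.000 | 80.1% | 0 | 80.0% | 80.0% |
| 0.60 | 0.978 | 81.0% | 13 | 81.3% | 81.3% |
| 0.635 | 0.957 | 81.8% | 27 | 80.1% | 81.6% |
| 0.68 | 0.920 | 83.3% | 51 | 81.0% | 83.7% |
| 0.71 | 0.889 | 84.5% | 73 | 80.1% | 83.7% |
| 0.74 | 0.856 | 85.9% | 99 | 80.3% | 86.1% |

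The Monte Carlo standard error is √(0.8·0.2/8000) = 0.4 points. At 0.60 the gain is within simulation noise; at 0.74 it is not.

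**3. What donor pairing changes.** Donors are randomized and may give one or two kidneys (Randomization and blinding), while recipients are counted (Sample size). If every donor gave two kidneys and the within-donor correlation were 0.10 (an assumption), the design effect would be 1 + (2 − 1)·0.10 = 1.10. The effective n is then 294/1.10 = 267 per group, and crude power is 76.3%.

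A simulation used 147 two-kidney donors per group, four donor and two recipient covariates (risk-score SD 0.5 to 0.75 on the logit scale) and an assumed residual donor effect of SD 0.6 to 0.9. An adjusted logistic model with ordinary standard errors had a type I error of about 6% to 7%. With donor-robust errors its power was 77% to 80%. So adjustment needs clustered errors, and the percentages in the table do not carry over as absolute power.

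**4. Which covariates qualify.** Baseline here is donor randomization.
- Donor age, diabetes and hypertension are fixed before it and are listed under Data registration.
- Recipient dialysis duration is listed, but the recipient may be matched to the kidney after the donor has been randomized.
- Recipient weight is not listed by name; BMI is.
- Donor norepinephrine is not listed by name. The nearest donor item is a detailed SOFA score over the last 24 h before harvesting. Study drug is given within the last 2 h before harvesting (Trial intervention), so that window can run past randomization.
- Cold and warm ischemia durations arise after randomization.

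**The case against.** The strongest reply is that this is a preference and not an error. An unadjusted test is not biased by omitting prognostic covariates, its error rate already allows for chance imbalance in them, and it matches the sample-size calculation exactly. That stands. A reader might infer from the concern that the crude result would be biased or invalid for lack of covariates; nothing in the documents supports that.

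A reader might also infer that the trial has almost no margin, because 294 barely exceeds 293.2. That overlooks the 648 to be recruited. The 10% allowance covers loss on primary or secondary endpoints, and DGF is read by day 7, so some recipients lost by 1 year would still count. Crude power could reach 83.8% under independence, though a design effect of 1.10 would bring 324 per group back to 324/1.10 = 294.5, about 80%.

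Third, the gain rests wholly on an assumed c-statistic and could be about one point. That stands too, and it is why the range is shown.

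Finally, not every variable named in the risk-factor model can simply be moved into the primary analysis. This is correct and shapes the fix. None of these replies shows a benefit from leaving the donor covariates out: with no prognostic value at all, power stays at 80%.

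**Conclusion.** The point holds as one of efficiency. The primary test is fixed as crude, the plan names and records usable baseline predictors, and the secondary model is not stated to give an adjusted treatment effect.

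The size is modest: from about 80% to about 81% to 86% power at 588 recipients, equivalent to roughly 13 to 99 more recipients. This assumes independent recipients and a joint c-statistic of 0.60 to 0.74. The three donor covariates alone may sit towards the lower end, since they are only part of the named set. Within-donor correlation lowers absolute power for crude and adjusted analyses alike.

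**What to change.** Before unblinding, state the primary analysis as a logistic model with treatment, donor age, donor diabetes and donor hypertension. Use donor-clustered standard errors (robust or GEE). Report the standardized (marginal) risk difference with its 95% confidence interval, so that the target stays the 10-point difference used for sizing. Keep the chi-square or Fisher comparison as a sensitivity analysis.

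Further covariates:
- Recipient dialysis duration and BMI may be added, with the stated assumption that kidney allocation and recipient inclusion are blind to treatment.
- Donor norepinephrine may be added only if its value before randomization is recorded.
- Cold and warm ischemia durations should stay out of this model.

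For the three donor covariates the cost is a change of analysis wording, a simple rule for missing values and slightly more analysis work. No extra recipients or data items are needed. Adding norepinephrine could require a new data item.

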## Methods/design

### Trial design

“Cis-A-Rein” is an investigator-initiated, prospective, multicenter, double-blind, randomized controlled versus placebo study performed to assess the effects of a donor preconditioning with cyclosporine A on kidney grafts function in transplanted patients. After randomization, cyclosporine A or a placebo will be given to brain-dead patients with a beating heart before organ harvesting. The function of the kidneys procured from these patients will be analyzed in the recipients of this graft. The study protocol was designed using the recommendations of the Consolidated Standards of Reporting Trials (CONSORT) Statement. It is described as required by the SPIRIT guidelines to ensure consistent reporting of clinical trials (Additional file 1). Figure 1 reports the overview of the enrollment, interventions and assessments of the trial.

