### Randomization and blinding

Computer-generated randomized lists will be drawn up before the onset of the study using a permuted block design, under the responsibility of the Clinical Research Unit (Unité Aide Méthodologique à la Recherche Clinique, AP-HM, France). Randomization (1:1 allocation ratio) will be stratified by center (*n* = 16) and the number of kidneys per donor (two modalities, one or two). Randomization is centralized, web-based and accessible 24 h a day according to the allocation list. A randomization number will be allocated to each patient. The intensivist and the nurse in charge of the donor with a beating heart will be blinded regarding the allocation of treatment (preparation by an intensive care unit (ICU) nurse or a clinician not in charge of the donor). The statistician, the transplanted patients and the clinicians in charge of the transplanted patient will all be blinded concerning the treatment allocation.

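### Donors are randomized, but delayed graft function is compared between recipients with a test that assumes independence; the nominal 5% level is exceeded if outcomes are positively correlated within donor

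*Protocol article*

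**What the plan says.** All references are to the Protocol article.

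- **Unit randomized and treated.** Trial design: "After randomization, cyclosporine A or a placebo will be given to brain-dead patients with a beating heart before organ harvesting". Each donor receives one dose.
- **Unit analysed.** Trial design: "The function of the kidneys procured from these patients will be analyzed in the recipients of this graft". The Sample size section counts recipients: 588 evaluable (294 per group), 648 with allowance for loss.
- **Recipients per donor.** Randomization and blinding gives the second stratification factor as "the number of kidneys per donor (two modalities, one or two"). Selection of participants lists "Indication of double kidney transplantation" as a recipient exclusion. Two included kidneys from one donor therefore go to two different recipients, both in that donor's arm.
- **Primary test.** Data analysis: "These proportions will be compared using the chi^2^ test or Fisher’s exact test for categorical variables (primary analysis"). Sample size sets the "threshold for statistical significance set at a *p* value of 0.05 (two-sided alpha").
- **Other analyses.** Sample size also says "Secondary outcomes will be compared between the two groups", by chi-square, Fisher's or Student's t test. The secondary logistic model lists donor, procurement and recipient covariates, but no donor cluster term.

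Nothing in the available text mentions clustering, an intraclass correlation or a design effect. The number of kidneys per donor is used only to stratify.

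**The concern.** Randomizing donors and measuring recipients makes each donor a cluster of one or two. Chi-square, Fisher's and t tests take their variance from independent recipients. If the two recipients of a donor tend to do well or badly together, the difference between arms varies more from trial to trial than that variance allows, and the nominal 5% test rejects too often under the null.

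The plan gives reason to expect such correlation. Data analysis names donor age, norepinephrine use, diabetes and high blood pressure as potentially linked to DGF, and both recipients of a donor share all four. At stake are the single primary p-value, which could not be taken at face value in a borderline positive trial, and the stated 80% power.

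This is not a detail left to an analysis plan. The article names a primary method, and that method does not fit the unit of randomization.

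**Working it through.** **1. The plan's own figure.** Inputs from Sample size: 30% versus 20% DGF, two-sided alpha 0.05, power 80%. With pooled variance and no continuity correction:

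n per group = [1.96 × √(2 × 0.25 × 0.75) + 0.8416 × √(0.30 × 0.70 + 0.20 × 0.80)]² / 0.10²
= (1.2002 + 0.5119)² / 0.01 ≈ 293.2, rounded up to 294.

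This is the stated 294 per group, 588 in all, so the design effect used was 1. The step to 648 is the loss allowance: 294 × 1.10 = 323.4, rounded up to 324 per group. It contains nothing for clustering.

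**2. Design effect.** For clusters of size m, DE = 1 + ICC × Σm(m−1)/Σm. With m equal to 1 or 2, the ratio is the share q of recipients whose co-recipient is also in the trial. Hence DE = 1 + q × ICC, which cannot exceed 1 + ICC.

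**3. Assumptions.** The article gives neither ICC nor q. Assumed ranges are ICC 0.05 to 0.5 and q 0.5 to 1.0.

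**4. Formulas.**
- True type I error of the planned test = 2 × [1 − Φ(1.96/√DE)].
- Power of a donor-adjusted test: the formula in step 1 with 294/DE per group.
- Evaluable recipients for 80% power: 294 × DE per group, rounded up, doubled.

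Example with q = 1 and ICC = 0.3: DE = 1.30; 1.96/√1.30 = 1.719; type I error 8.6%. The effective n is 294/1.30 = 226 per group, and power is Φ[(0.10 × √226 − 1.2002)/0.6083] = 69.1%.

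| q | ICC | DE | Type I error | Adjusted power at 588 | Evaluable N for 80% |
|---|---|---|---|---|---|
| 0.5 | 0.05 | 1.025 | 5.3% | 79.1% | 604 |
| 0.5 | 0.1 | 1.05 | 5.6% | 78.2% | 618 |
| 0.5 | 0.3 | 1.15 | 6.8% | 74.4% | 678 |
| 0.5 | 0.5 | 1.25 | 8.0% | 70.8% | 736 |
| 0.8 | 0.05 | 1.04 | 5.5% | 78.6% | 612 |
| 0.8 | 0.1 | 1.08 | 5.9% | 77.0% | 636 |
| 0.8 | 0.3 | 1.24 | 7.8% | 71.2% | 730 |
| 0.8 | 0.5 | 1.40 | 9.8% | 65.9% | 824 |
| 1.0 | 0.05 | 1.05 | 5.6% | 78.2% | 618 |
| 1.0 | 0.1 | 1.10 | 6.2% | 76.3% | 648 |
| 1.0 | 0.3 | 1.30 | 8.6% | 69.1% | 766 |
| 1.0 | 0.5 | 1.50 | 11.0% | 62.9% | 882 |

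**5. Simulation check.** With 200,000 null trials per setting, 294 recipients per arm and a common rate of 25%, the ordinary chi-square rejects in 6.1%, 8.6% and 11.0% at ICC 0.1, 0.3 and 0.5 when q = 1, and in 5.6%, 6.8% and 8.0% when q = 0.5. This agrees with the formula.

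**The case against.** The strongest case on the other side is about size, and much of it stands.

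- **Sharing a donor is not enough.** The inflation needs positive within-donor correlation, and no ICC is given. The list in Data analysis also includes recipient weight, dialysis duration and ischemia times, which can differ between co-recipients and limit the correlation.
- **The upper end is strong.** At a 25% rate, ICC 0.5 means a risk of 0.25 + 0.5 × 0.75 = 62.5% if the co-recipient had DGF and 0.25 − 0.5 × 0.25 = 12.5% if not, an odds ratio of about 12. Nothing in the article supports a value that high.
- **Many second kidneys may fall outside the trial.** Some donors supply only one kidney. Each recipient must also meet the age limits, consent, and need neither a double nor a multiorgan transplant. At q = 0.5 and ICC 0.05 the error is only 5.3%.
- **There are offsets.** Randomization is stratified, but the test ignores the strata, which pulls in the conservative direction; Fisher's test is itself conservative. The article does not allow either to be quantified, so the tabulated figures are not net inflation.

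Two stronger readings are tempting. A reader might infer that the primary confidence interval is too narrow, but the article specifies none; the point reaches only an interval computed on the same independence basis. A reader might also infer that every secondary comparison is affected. That depends on the outcome: within-donor correlation could be near zero for length of stay or recipient mortality, and time to normalization is analysed only in patients with DGF, where few complete pairs may remain.

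None of this makes an independence test fit donor-randomized data.

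**Conclusion.** The mismatch between unit of randomization and unit of analysis is established by the text. The anti-conservative effect is conditional on positive within-donor correlation, which the plan's own list of donor factors makes plausible but does not quantify. Over the assumed ranges, the nominal 5% test has a true type I error of about 5.3% to 11%, before the offsets. The effect is bounded because a cluster has at most two members, and it may be small.

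The same assumption affects the secondary recipient-level tests and the logistic model wherever the outcome is correlated within donor. The stated 80% power holds only under independence; a donor-adjusted test at 588 has about 63% to 79% over the same ranges.

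A reader might conclude that the p-value is too optimistic whenever a donor supplies two recipients. The documents do not support that: with zero correlation the planned test keeps its level.

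**What to change.** 1. **Primary analysis.** Replace the chi-square or Fisher's test by one donor-clustered marginal comparison, for example a GEE with donor as cluster and robust variance. Pre-specify one effect measure, such as the risk difference, and adjust for the stratification factors where feasible. Naming one measure matters because marginal and random-intercept models estimate different quantities. Clusters are numerous enough for a robust variance: 588 × (1 − q/2) gives 294 donors at q = 1 and 441 at q = 0.5.
2. **Other analyses.** Use donor-clustered variance for the secondary recipient-level outcomes and the multivariable model.
3. **Data.** Keep the donor identifier on every recipient record.
4. **Sample size section.** Restate the power with an assumed ICC and pairing share. The 10% allowance is already committed to loss and cannot also cover clustering.

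**Cost.** Items 1 to 3 change wording before unblinding and need no new data if the donor identifier is kept. An interval would be wider by a factor of √DE, about 1% to 22% over the assumed ranges. Item 4 makes the stated power less favourable; holding 80% would take 604 to 882 evaluable recipients. If the true ICC is near zero, the adjusted result will hardly differ from the planned one.
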